### Outcomes

#### Primary outcome measures

*Feasibility measures*: This includes feasibility of the intervention and feasibility of the trial measures. These data will be collected throughout the trial by researchers and used to inform the feasibility of conducting a future RCT.

*Feasibility of intervention measures*: This includes adherence to the intervention and qualitative information on acceptability and feasibility.

*Feasibility of trial measures*: This will consist of numbers approached/numbers consented and randomised, errors in randomisation, drop-out rates at each time point, outcome measure completion rates, instances of unblinding, and protocol deviations.

*Pilot outcome*: The variance of the change in *Patient Health Questionnaire modified for adolescents (PHQ-A)* [38] from baseline. PHQ-A is adapted from the PHQ-9 and modified for adolescents. It is a 9-item measure with each measure rated on a 4-point scale that assesses the severity of depressive disorders and episodes) in children and adolescents. The measure is completed by the adolescent. Each item asks the adolescent to rate the severity of their depression symptoms during the past 2 weeks. The total score can range from 0 to 27, with higher scores indicating greater severity of depression. There are four additional items which relate to difficulties performing everyday tasks, suicidal thoughts, and attempts; however, these are not scored. The questionnaire has established validity and reliability [38]. A 5-point change is viewed as clinically significant [46]. The PHQ-A was chosen as the primary outcome measure, as this was the preferred option of our patient and public involvement (PPI) group over other commonly used measures of depression.

#### Other outcome measures

*Revised Child Anxiety and Depression Scale (RCADS)* [47]: The RCADS is a 47-item self-report questionnaire that measures symptoms of depression and anxiety in children and adolescents. The RCADS consists of six subscales helpful in screening children and adolescents for high prevalence disorders, including separation anxiety disorder, social phobia, generalised anxiety disorder, panic disorder, obsessive compulsive disorder (OCD), and major depressive disorder. A Total Anxiety Scale score (sum of the five anxiety subscales) and a Total Internalizing Scale score (sum of all six subscales) are derived, with higher scores indicating increased symptom severity. The RCADS has demonstrated good structural validity, reliability, and convergent and discriminant validity [47]. The RCADS is a widely used instrument within CAMHS and MHSTs.

*EQ-5D-Y and EQ-5D-Y (Proxy version)* [48, 49]: The child-friendly EQ-5D version (EQ-5D-Y) was introduced by the EuroQol Group in 2009 as a more comprehensible instrument suitable for children and adolescents and is based on the EQ-5D-3L. The EQ-5D-Y comprises the following five dimensions: mobility, looking after myself, doing usual activities, having pain or discomfort, and feeling worried, sad, or unhappy. Each dimension has three levels: no problems, some problems, and a lot of problems. The adolescent is asked to indicate his/her health state by selecting the most appropriate statement in each of the five dimensions. This decision results in a 1-digit number that expresses the level selected for that dimension. The digits for the five dimensions can be combined into a 5-digit number that describes the adolescent’s health state. The EQ VAS records the adolescent’s self-rated health on a vertical visual analogue scale where the endpoints are labelled “The best health you can imagine” and “The worst health you can imagine”. The EQ-5D-Y (Proxy version) asks the caregiver (the proxy) is to rate the child’s/adolescent’s health-related quality of life in their (the proxy’s) opinion. Both measures have established validity and reliability [48, 49] and will be used in this study to measure health related quality of life.

*Clinical Global Impressions Scale (CGI)-Severity/Improvement* [50]: The CGI provides an overall clinician-determined summary measure that considers all available information, including a knowledge of the patient’s history, psychosocial circumstances, symptoms, behaviour, and the impact of the symptoms on the patient’s ability to function. The CGI comprises two companion one-item measures evaluating the following: (a) severity of psychopathology from 1 to 7 and (b) change from the initiation of intervention on a similar 7-point scale. The CGI-S asks one question: “Considering your total clinical experience with this particular population, how mentally ill is the patient at this time?” which is rated on a 7-point scale (from 1 = normal, not at all ill to 7 = amongst the most extremely ill patients). The CGI-I consists of one item: “Compared to the patient’s condition at admission to the project this patient’s condition is…” and is rated from 1 = very much improved since the initiation of intervention to 7 = very much worse since the initiation of intervention. The questionnaire has established validity and reliability and is widely used in clinical research [51].

*Concomitant interventions*: To assess what other mental health treatments/interventions the adolescent is accessing during the study period, parents/guardians will be asked to complete a short questionnaire, which asks about current diagnoses and treatments/interventions/medication in progress. This will be completed at baseline as part of the demographic questionnaire completed with the researcher and then again at 8–10-week follow-up with the researcher via telephone/Microsoft Teams.

*Usage data*: Indices such as number of modules completed, time spent using SPARX, and number of logins will be collected via an in-built SPARX feature, and time spent with e-coaches (if in supported arm) will be recorded in REDCap. These data will be collected throughout the trial and will be used to measure adherence and engagement as part of the process evaluation.

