#### Screening

After the research team receive consent to contact and the associated contact details, they will arrange a telephone/videoconferencing screening appointment with the parent/guardian or adolescent (if they are 16 years and over). This screening approach has shown to be effective in previous trials of similar interventions [42, 43]. At this point, the following details will be recorded: contact details, age of depression onset and brief clinical history, previous contact with healthcare services, previous/current medications or therapy for depression, access to Internet/PC/Mac/laptop/smartphone, other diagnoses, and inclusion/exclusion criteria. The researcher will outline the time commitment involved in the trial at this stage. Adolescents meeting any exclusion criteria or not meeting all inclusion criteria at this time point will not be invited to the baseline assessment. If the adolescent is not eligible for the study or does not wish to attend a baseline appointment, the researcher will record the reason for nonparticipation. Reasons for not attending a baseline assessment will be recorded for CONSORT reporting.

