##### Exclusion criteria

Adolescents will not be able to enter the study if ANY of the following apply:Clinical concerns that depression is too severe to benefit from SPARX and self-harm/suicidal risk is too highIntellectual disability or physical limitations precluding the use of SPARX (confirmed at baseline via CAIDS-Q)Had (in past 3 months) or currently having treatment with CBT/interpersonal therapy (confirmed at baseline)Has another major mental health disorder (e.g. psychosis, eating disorder) where the primary focus was not depression as confirmed by a clinician or DAWBASafeguarding concerns that are not currently being managed (i.e. the adolescent is the subject of a safeguarding investigation) as confirmed by a clinician

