### Waitlist control group

The control group is a waitlist group. They will mostly be on waiting lists for services and will not have access to the SPARX intervention; however, they may receive support from other sources which we will capture at the primary endpoint via the concomitant interventions measure. Adolescents will receive £20 worth of Amazon vouchers for each assessment time point completed.

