#### Process evaluation

The process evaluation will follow the Medical Research Council’s (MRC) guidelines for evaluating complex interventions [57]. It will explore the components suggested in MRC guidelines, namely reach, dose, and fidelity of implementation of intervention, and make recommendations for adaptations for the future RCT. It will also examine the contextual factors and potential mechanisms underlying participant behaviour change and probe for any unexpected consequences.

Interviews will be conducted with adolescents assigned to either version of SPARX (target *n* ≥ 30) and parents/guardians of adolescents (*n* ≥ 30) after they have completed their 8–10-week follow-up. This sample size will be determined based on the model of information power where we will aim to achieve both breadth and depth of views [58]. Purposive sampling will be used so that a diverse range of views are voiced, including diversity in terms of ethnicity, socioeconomic status, and adherence to the intervention (i.e. interviewing those who completed 0 level to treatment completers). Interviews with e-coaches supporting the intervention (target *n* ≥ 3) and clinicians recruiting to the study (*n* ≥ 5) will be conducted during trial delivery. Online feedback from participants will also be analysed together with usage indices recorded as part of the online system such as total time spent with e-coach, number of modules completed, and number of logins. A brief online questionnaire will be given to participants who drop out of the trial early to gain a more holistic overview of engagement with SPARX. A full process evaluation protocol will be published.

Table 2 outlines the completion time points for each outcome measure and who completes them.

**Table 2 Tab2:** Baseline and outcome measures

Months post-randomisation	0	0	1	2
Time point	Telephone/videoconference screening	Baseline	Mid-intervention (4 weeks)	Primary end point (8–10 weeks)
Consent		R (P+A)		
Randomisation		R		
PHQ-A		R (A/P)	A/P	R (A/P)
CAIDS-Q		R (A/P)		
RCADS		R (A/P)		R (A/P)
Screening for eligibility	R (P)	R		
SDQ & DAWBA (conducted post telephone/videoconference screen & prior to baseline)	P			
CGI-S/I		R (A/P)		R (A/P)
EQ-5D-Y		R (A)		R (A)
EQ-5D-Y (proxy version)		R (P)		R (P)
Demographics		R (A/P)		
Concomitant interventions		R (A/P)*		R (A/P)
Adverse events		R (A/P)	A/P	R (A/P)
Interview (process evaluation)				R

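### As described, the concomitant-interventions form records treatment under way at two visits, although its stated purpose is treatment used over the whole study period

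*Protocol article*

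**What the plan says.** Under Other outcome measures, the protocol article gives the purpose of the concomitant-interventions measure: "To assess what other mental health treatments/interventions the adolescent is accessing during the study period". It then describes a short questionnaire for parents or guardians, "which asks about current diagnoses and treatments/interventions/medication in progress". On timing, the first administration is at baseline, inside the demographic questionnaire, and the form is given "then again at 8–10-week follow-up with the researcher via telephone/Microsoft Teams".

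Table 2 agrees. The concomitant-interventions row has entries under baseline and the primary end point only. Its 4-week cell is empty, although the PHQ-A and adverse events are collected at that time.

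The Waitlist control group section relies on the same measure. It says of the controls that "they may receive support from other sources which we will capture at the primary endpoint via the concomitant interventions measure", and it names no other source.

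**The concern.** The purpose covers an interval, but the form as described records status at two points. An episode of counselling, a short course of therapy or a trial of medication that begins after baseline and ends before the 8–10-week contact is in progress at neither visit. A respondent who answers the described question literally would not report it.

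This bears on what the pilot is for. The Discussion says the later trial will compare SPARX with care as usual. What waitlist participants actually received, and how much other treatment SPARX participants used alongside it, are therefore planning inputs. Controls are expected to be mostly waiting for services, so some may well begin other care during follow-up. An under-count would make the control condition look less treated than it was, and the same could happen in either SPARX arm. An analysis plan cannot recover information that the form did not ask for.

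**Working it through.** The plan states no figure on this point, so there is none to reproduce. The check is first a comparison of passages and then an illustration under stated assumptions.

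**1. Purpose against content.** The purpose in Other outcome measures is treatment accessed during the study period. The content in the same paragraph is treatment in progress. The form is given at two times, baseline and 8–10 weeks, and Table 2 confirms this.

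**2. What two such snapshots record.**

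| Course of treatment | In progress at baseline | In progress at 8–10 weeks | Captured as described |
|---|---|---|---|
| Running at baseline, stops during follow-up | yes | no | yes, at baseline |
| Starts during follow-up, still running at the end | no | yes | yes, at 8–10 weeks |
| Running throughout | yes | yes | yes |
| Starts and stops between the visits | no | no | no |

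Only the last row is lost.

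**3. Does another source fill that row?**
- Screening records "previous/current medications or therapy for depression", but this comes before randomisation and says nothing about the follow-up interval.
- The process-evaluation interviews are with adolescents in the two SPARX arms and their parents or guardians (target at least 30 of each). They are a purposive, qualitative sample with no control-arm interviews described.
- The week-4 contact collects the PHQ-A and adverse events, not other treatment.
- The article describes no look-back question and no review of records for treatment received during follow-up.

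**4. Illustration of how the loss depends on duration.** Assumptions, none of them from the documents: an episode starts at a time uniform on (0, T) after baseline, lasts D weeks, and is recorded only if still running at T. It is missed when its start falls before T − D, so

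share missed = max(0, (T − D)/T).

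| D (weeks) | T = 8 | T = 10 |
|---|---|---|
| 2 | (8−2)/8 = 75% | (10−2)/10 = 80% |
| 4 | (8−4)/8 = 50% | (10−4)/10 = 60% |
| 6 | (8−6)/8 = 25% | (10−6)/10 = 40% |
| 8 | 0% | (10−8)/10 = 20% |
| 10 or more | 0% | 0% |

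These are shares of new episodes, not of participants. Turning them into an under-count per arm needs the number and length of new episodes, which the documents do not give. With a question covering everything since baseline, the share missed by design is 0% for every D, leaving only recall error.

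**5. Does the form enter the pilot outcome?** No. The pilot outcome is the variance of change in PHQ-A, which is calculated from PHQ-A scores. Statistical methods describes summary statistics and says that variance, not effect, is being estimated.

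**The case against.** The strongest reply is that the questionnaire itself is not shown. One sentence in a journal article paraphrases it, and item wording, recall window and dates normally sit in the case report form. The stated purpose, and the promise to capture at the endpoint the support that controls receive, can be read as implying a retrospective account. A researcher also takes the follow-up by telephone or video and could probe. This stands in part: a reader might infer that short episodes are certain to go unrecorded, and the documents do not establish that. The mismatch remains, because the article does not merely omit a recall window. It describes content that does not fit the aim stated in the same sentence.

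A reader might also infer that the entry rule contradicts the form, because it excludes an adolescent who "Had (in past 3 months) or currently having treatment with CBT/interpersonal therapy (confirmed at baseline"). It does not. That is an eligibility look-back applied at baseline and the form describes care during follow-up, so neither statement negates the other.

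A third reply is that little depends on this in a descriptive pilot. That is largely right. If the later comparator is care as usual, outside treatment also belongs in the variance being estimated. What is at stake is the description of background care.

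**Conclusion.** The point holds in a limited form. As described, the form's content does not match its stated purpose, and treatment that both starts and stops between baseline and 8–10 weeks would not be captured. Background care in any of the three arms could then be under-counted when the definitive trial is planned. The conclusion assumes that the questionnaire follows the article's description.

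The size cannot be determined. The illustrative shares run from 80% of 2-week episodes to none of those lasting 10 weeks or more, and they rest wholly on an assumed uniform start and assumed durations.

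Stronger conclusions are not supported. The estimate of PHQ-A variance does not use the form, and no hypothesis test depends on it. A difference in under-counting between arms is possible, but nothing in the documents shows one.

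**What to change.** Word the 8–10-week form, in all three arms, to ask about any mental health treatment, intervention or medication received since the baseline appointment, whether ongoing or stopped. Record the type and the start and stop dates, and report the results by arm. Align the Waitlist control group section and the concomitant-interventions paragraph so that both refer to this record. If the questionnaire in use already looks back to baseline, leave it unchanged and correct the paragraph that describes it.

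The cost is a rewording of one existing form at an existing contact, one or two more minutes of interview, and a short descriptive table. The downside is some recall error over 8–10 weeks. Visits, eligibility, treatment and sample size do not change. A second PHQ-A standard deviation that leaves out participants who received other treatment is not needed: it would condition on events after randomisation in arms of about 40 and would not serve the stated pilot objective.

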#### Adverse events

Adverse events/side effects will be recorded by the PHQ-A and on a modified version of the side effects scale developed by Hill and Taylor [52]. An adverse event will be recorded where there is clinically meaningful deterioration from baseline on the PHQ-A. On the PHQ-A, a > = 5-point increase (i.e. moving one severity category) is regarded as clinically meaningful [46], and thus, an adverse event will be recorded when this occurs or where there is an increase of one, or more, point from baseline to follow-up (4 weeks and/or 8–10 weeks) on item 9 or a positive response (i.e. “yes”) on any of the two additional suicide items from baseline to follow-up. The Hill and Taylor [52] scale consists of 17 short items relating to common side effects (such as headaches, anxiety, sleep, and low mood). The participant is asked to respond on a 5-point scale ranging from “not at all” to “all the time” to describe the presence of each item. A score on any item that is equal to or greater than 2 (“about half the time”) and greater than their baseline score is recorded as an adverse event on this scale. All adverse events/side effects will be captured at baseline (to ascertain presence of these symptoms prior to the intervention), mid-intervention, and 8–10-week follow-up.

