#### Safeguarding and participant care

No significant risks to physical safety are anticipated; however, changes in depressive symptoms may occur in adolescents during the trial and cause psychological harm. Although a formal data monitoring committee is not required due to the minimal physical risks associated with the intervention, we will have an independent scientific advisory board, which serves a similar function to a Trial Steering Committee (TSC), throughout the trial. To ensure participant safety, adverse events will be recorded at baseline, 4 weeks, and 8–10 weeks. Any related or unexpected serious adverse events will be reported to the research ethics committee.

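### The scored PHQ-A items that define adverse events leave 33–60% of post-randomisation time unobserved, and the article does not show that its other instruments cover those weeks

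*Protocol article*

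**What the plan says.** The Adverse events section names two sources: "Adverse events/side effects will be recorded by the PHQ-A and on a modified version of the side effects scale". For the first, "An adverse event will be recorded where there is clinically meaningful deterioration from baseline on the PHQ-A", meaning a rise of 5 points or more in the total. A rise of one point or more on item 9 also counts, as does "a positive response (i.e. “yes”) on any of the two additional suicide items from baseline to follow-up". For the second, the "scale consists of 17 short items relating to common side effects (such as headaches, anxiety, sleep, and low mood"; an item counts when it scores 2 or more (present roughly half of the time) and exceeds its baseline score.

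Timing is given under Safeguarding and participant care: "To ensure participant safety, adverse events will be recorded at baseline, 4 weeks, and 8–10 weeks". Table 2 shows the same three points for both the PHQ-A and adverse events.

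Recall is given under Primary outcome measures: "Each item asks the adolescent to rate the severity of their depression symptoms during the past 2 weeks". The suicide items are among the PHQ-A's unscored extras: "There are four additional items which relate to difficulties performing everyday tasks, suicidal thoughts, and attempts; however, these are not scored". No recall period is stated for these extras or for the side effects scale.

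The follow-up clock is described in two ways. The Abstract and the header of Table 2 count from randomisation, while Trial design and Trial setting count from baseline. The section on the baseline and consent appointment allows up to 2 weeks between the two.

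**The concern.** A questionnaire with a 2-week recall, given at two follow-up visits, sees two 2-week windows. Depressive symptoms and suicidal thoughts can come and go. An episode that begins and ends between the windows changes neither the PHQ-A total nor item 9 at the visit, so it meets neither of those two rules. In the supported arm modules are released at one or two per week, so seven modules take 7/2 = 3.5 to 7/1 = 7 weeks; a gap can therefore fall during active use.

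What is at stake is how complete the pilot's harm record is in depressed adolescents from age 11. The trial version of SPARX has no in-app measures that would pick up such an episode. Table 2 marks the week-4 assessment as completed by the adolescent or parent, without a researcher.

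**Working it through.** The article gives no coverage figure, so there is none to reproduce. The check is interval arithmetic.

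**Inputs**
- Recall of the scored PHQ-A items, r = 2 weeks (Primary outcome measures).
- Follow-up visits at week 4 and at week E, with E = 8 to 10 (Adverse events; Table 2; Safeguarding and participant care).
- Lag from baseline to randomisation, L = 0 to 2 weeks (section on the baseline and consent appointment). L matters only if visits are timed from baseline. If they are timed from randomisation, set L = 0.

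**Formulas** (weeks after randomisation)
- The visits fall at 4 − L and E − L, and each covers the r weeks before it.
- First gap = (4 − L) − 2 = 2 − L.
- Second gap = (E − 2) − 4 = E − 6. It does not depend on L.
- Fraction unobserved = (first gap + second gap) / (E − L).

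**Results**

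| L | E | First gap | Second gap | Unobserved |
|---|---|---|---|---|
| 0 | 8 | 2 | 2 | 4/8 = 50% |
| 0 | 9 | 2 | 3 | 5/9 = 56% |
| 0 | 10 | 2 | 4 | 6/10 = 60% |
| 1 | 8 | 1 | 2 | 3/7 = 43% |
| 1 | 10 | 1 | 4 | 5/9 = 56% |
| 2 | 8 | 0 | 2 | 2/6 = 33% |
| 2 | 10 | 0 | 4 | 4/8 = 50% |

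With L = 0 the unobserved weeks are 0–2, plus 4–6 (visit at week 8) or 4–8 (visit at week 10). The second gap is 2 to 4 weeks on every reading of the clock.

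**Could the other sources fill the gaps?** Their recall is not stated, so the values below are assumptions, with L = 0.
- A recall of 1 week would leave 6 of 8 weeks (75%) to 8 of 10 weeks (80%) unobserved.
- A recall of 4 weeks would leave nothing unobserved with a visit at week 8, and weeks 4–6 (2 of 10, 20%) with a visit at week 10.
- A recall reaching back to the previous assessment would leave nothing unobserved.

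The side effects scale also has a frequency threshold. If its window were the whole 4 to 6 weeks between assessments (an assumption), symptoms present every day for 2 weeks would fill 2/4 = 50% to 2/6 = 33% of it. That is at or below the half-of-the-time level needed to count.

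**The case against.** The strongest case against is that the PHQ-A is not the only detector. The side effects scale includes low mood and anxiety, and a positive answer on either suicide item counts. A recall period that is not stated is not thereby 2 weeks. This is a condensed article; the wording of the adverse-event form and any route for spontaneous reports may stand in the full protocol. The statement that related or unexpected serious adverse events go to the ethics committee implies that someone learns of them. At the endpoint every arm also has a CGI improvement rating and a questionnaire on concomitant interventions.

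Much of this stands, and it limits what can be said. A reader might infer that episodes in the gaps go unrecorded altogether; that is shown only for the scored items. A reader might infer that recorded rates must be too low, but the rules are otherwise sensitive (one point on item 9, or any one of 17 side effect items), so the net direction of error is not established. A reader might also infer that the self-directed and waitlist arms have no way to report, or that e-coach contact distorts the comparison between arms. The article supports neither: adverse events are defined by instruments put to all arms at the same times, and nothing says that e-coach reports are counted. Nor does it say that the definitive trial will rely on these harm rates; the stated objectives are feasibility, adherence and the variance of PHQ-A change.

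What does not stand is that the point is mere silence. The article fixes the instruments, the PHQ-A recall and the capture times, and these together create the gaps. The concomitant interventions questionnaire is asked only at baseline and the endpoint and concerns treatments in progress, so a crisis contact that has ended need not appear.

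**Conclusion.** The point holds for the scored PHQ-A items. They leave 50–60% of follow-up unobserved if visits are timed from randomisation, and 33–50% of post-randomisation time if visits are timed from baseline and randomisation follows 2 weeks later. At least a third is unobserved on every reading, and no instrument described in the article is shown to cover it. A deterioration or self-harm event confined to those weeks may be missed, and recorded harm may be too low by an amount the article does not allow one to estimate.

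This assumes that visits occur on schedule and that adolescents answer strictly for the past 2 weeks. An episode that runs into a recall window could still be picked up. If the side effects scale and the suicide items prove to ask about the whole time since the last assessment, the point shrinks to general deterioration too brief to meet the side effects threshold.

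**What to change.** At the existing week-4 and 8–10-week adverse-event assessments, put one identical question to all three arms, covering the whole time since the previous assessment: any self-harm, suicide attempt, emergency or crisis contact, or marked worsening, with its date. By design this leaves no week uncovered, and the dates separate events before randomisation from those after it.

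State the recall period of the side effects scale and of the two additional suicide items. Reconcile the passages that count follow-up from randomisation with those that count it from baseline, because the size of the first gap depends on this.

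The cost is one extra item at two contacts that already take place: slight added burden, and possibly a higher recorded adverse-event rate. The change concerns data collection only and alters no rule for participant care.
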